### 2.2. Study Timeline

The study will be conducted as a single randomized controlled trial with two pre-planned analytical phases applied to the same underlying dataset.

Phase 1 will include 156 participants and will evaluate the primary outcome comparing BATF and Brief Focal Psychotherapy with collapsed clinical conditions (anxiety and depression). This represents the primary confirmatory analysis of the trial.

Phase 2 will include the full sample (*n* = 472) and will perform a pre-specified 2 × 2 factorial analysis including intervention and clinical condition factors, incorporating all participants from Phase 1. Both analytical phases are pre-specified and independent, with no post hoc modifications to the analytical structure.

Recruitment is anticipated to begin in the fourth quarter of 2026. Recruitment will occur continuously throughout the study period until the target sample size for Phase 2 is reached. Recruitment for Phase 1 is expected to be completed by the fourth quarter of 2027. Intervention delivery and outcome assessments for Phase 1 are expected to be completed shortly thereafter. Recruitment for the full sample is expected to continue until completion of Phase 2, anticipated in the fourth quarter of 2029. Final data collection and database closure are expected following completion of participant follow-up.

### 2.3. Eligibility Criteria

#### 2.3.1. Type of Participants

Students at the Federal University of Rio Grande do Norte (UFRN) seeking outpatient treatment at the mental health unit, in the Psychiatry Division of the Department of Internal Medicine.

#### 2.3.2. Inclusion Criteria

Adults aged 18 years or older with a clinical diagnosis of anxiety and/or depressive disorders will be included in the study upon signing an informed consent form. The diagnosis will be established through a clinical evaluation conducted by trained clinical personnel according to DSM-5-TR diagnostic criteria prior to enrollment. If psychotropic medication is used, it must be used regularly, with no changes in medication type or dose during the 6 weeks preceding study entry. Information regarding medication type, dose, and duration of use will be recorded at baseline. Any medication changes occurring during the study will be documented and considered in sensitivity analyses when appropriate.

#### 2.3.3. Exclusion Criteria

Individuals who meet the following conditions will be excluded from the study: current substance use disorder (excluding alcohol and tobacco use disorders), tobacco use, alcohol use disorder, imminent risk of suicide, schizophrenia, psychotic symptoms, bipolar disorder, use of oral contraceptives, or pregnancy.

Eligibility criteria related to substance use, pregnancy status, medication use, and psychiatric comorbidities will be assessed through clinical interview, self-report, review of available medical information, and, when applicable, confirmation during the baseline clinical evaluation conducted by trained clinical personnel.

These criteria were adopted to minimize potential confounding factors that could influence clinical outcomes and the assessment of salivary and blood biomarkers, ensuring greater homogeneity of the sample and improving the internal validity of the trial.

Participants identified as being at imminent risk of suicide during baseline clinical assessment will not be enrolled and will be immediately referred for appropriate psychiatric care within the Mental Health Unit, including urgent psychiatric evaluation and follow-up when necessary.

### 2.4. Interventions

BATF, the experimental intervention in the present trial, will be delivered in a maximum of three sessions. BATF is an experimental psychotherapeutic intervention currently under evaluation in a randomized controlled trial, and has not yet been validated as an evidence-based treatment. Brief Focal Psychotherapy, which will serve as the active comparator group, may be conducted over a maximum of ten sessions, with sessions occurring once per week.

It is important to note that the difference in the number of sessions between BATF and Brief Focal Psychotherapy reflects the intrinsic structure and clinical logic of each intervention, and not an attempt to equalize treatment dose. BATF was designed as a highly structured, protocol-based brief intervention delivered in a maximum of three sessions, whereas Brief Focal Psychotherapy follows a more conventional brief psychotherapy format, typically delivered over several sessions. Therefore, the present trial compares two distinct models of brief psychotherapy as implemented in clinical practice, rather than interventions with pre-standardized or equivalent dose. This design allows for the evaluation of comparative effectiveness under real-world clinical conditions.

BATF will be implemented on the first day, followed by a second session after four weeks, and a third optional session nine weeks later, if all items from the previous session have not been completed. A follow-up psychotherapy session will be scheduled at week thirteen post-baseline for feedback and the collection of scales and clinical assessments. Session number and treatment duration were defined according to the theoretical and procedural characteristics of each intervention. The timing of BATF sessions was aligned with the predefined assessment schedule of the trial (baseline, 4 weeks, and 13 weeks), which includes clinical scales and biological sample collection (blood and saliva). The second BATF session at 4 weeks coincides with the first post-baseline assessment. The optional third session, scheduled nine weeks after the second session (corresponding to the week-13 follow-up visit), may be conducted when previously established therapeutic objectives have not yet been fully achieved. The 13-week study period was defined to allow completion of Brief Focal Psychotherapy, which may include up to ten sessions, while maintaining a common outcome assessment window for both study arms. This scheduling ensures temporal correspondence between psychotherapeutic intervention, clinical assessments, and biomarker evaluation.

Both the experimental psychotherapy and the standard psychotherapy will be conducted by qualified professionals. These professionals are trained to handle the entire psychotherapeutic process, from diagnosis and therapeutic guidance to clinical assessment of progress.

The severity and clinical progression of anxiety and depression will be assessed using well-established and validated clinical scales, together with biomarker analyses of blood and saliva samples. These biomarkers have been extensively investigated in the scientific literature regarding normal physiological ranges and alterations associated with anxiety and depressive symptoms. Therefore, it is important to monitor the levels of each biomarker evolutionarily, from diagnosis through to the end of the patient’s follow-up. Similarly, specific questionnaires for depression and anxiety are established scales for assessing symptom severity from diagnosis, as well as for tracking clinical improvement. The first collection of saliva and blood samples, as well as the administration of depression and anxiety scales, will be conducted prior to the start of psychotherapy to serve as baseline measurements. Subsequent assessments and sample collections will be conducted initially at 4 weeks and again at 13 weeks (Figure 1). Clinical scales and biomarker collections will be synchronized at each assessment time point to ensure temporal correspondence between clinical and biological measures.

Potential Harms, Clinical Deterioration, and Withdrawal Procedures:

As approved by the ethics committee and explained in the informed consent form, all research involving human participants carries some inherent risks, which will be minimized through continuous clinical monitoring during psychotherapy sessions and follow-up assessments.

Adverse Events (AEs):

Adverse events will include any unfavorable psychological, emotional, or clinical occurrence reported by the participant or observed by the therapist during the study period, regardless of direct attribution to the intervention. These may include transient emotional distress, increased anxiety, mood worsening, or discomfort during psychotherapeutic procedures.

Serious Adverse Events (SAEs):

Serious adverse events will include any clinically significant condition requiring urgent psychiatric intervention, hospitalization, emergency referral, substantial functional impairment, suicidal risk requiring immediate evaluation, or any event considered by the investigators to represent significant clinical risk.

Clinical Deterioration:

Clinical deterioration will refer to worsening of anxiety, depressive symptoms, emotional instability, or psychosocial functioning identified through clinical evaluation, psychotherapy sessions, or validated clinical scales during follow-up. If deterioration is suspected, participants may undergo additional diagnostic evaluation using the Structured Clinical Interview for DSM-5-TR (SCID-5-TR) and other clinically relevant assessments.

Clinical Management:

Should symptoms arise requiring pharmacological treatment or additional psychiatric support, psychiatric consultation will be available within the Mental Health Unit of the same institution. Each case will be individually evaluated, and appropriate clinical measures may include extension of psychotherapy, referral to long-term psychotherapy, psychiatric treatment, or other clinically indicated interventions.

Withdrawal Criteria:

Participants may be withdrawn from the study in cases of severe clinical deterioration, serious adverse events, emergence of psychiatric conditions requiring immediate alternative treatment, participant request, non-adherence to study procedures, or investigator judgment that continuation may compromise participant safety or study integrity.

Protocol Deviations:

All protocol deviations, including missed sessions, incomplete assessments, deviations from intervention procedures, or unplanned clinical management modifications, will be documented and reviewed by the investigators. Any clinically relevant deviation affecting participant safety or trial conduct will be reported to the ethics committee when required.

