## Abstract

Background: Brief psychotherapies have been shown to improve clinical symptoms within a limited number of sessions without compromising treatment quality. Objectives: This study aims to test the effects of the experimental Behavioral Analysis Therapy of Feelings (BATF) in a randomized controlled trial design. Methods: This randomized, controlled, assessor-blinded clinical trial compares BATF with Brief Focal Psychotherapy in individuals presenting symptoms of anxiety and/or depression. Participants with substance use disorders, tobacco or alcohol use, pregnancy, or use of oral contraceptives will be excluded. Participants will be randomized in a 1:1 ratio with stratification by clinical condition. Outcomes will be assessed at baseline, Week 4, and Week 13 using the Hamilton Anxiety Rating Scale, the Montgomery–Åsberg Depression Rating Scale, the Patient Health Questionnaire-9, the Generalized Anxiety Disorder-7, and the Pittsburgh Sleep Quality Index. In addition to clinical outcomes, exploratory salivary and blood biomarkers associated with stress, inflammation, and neurobiological function will be evaluated. The trial is registered in the Brazilian Clinical Trials Registry (RBR-10p45rdg) and has Universal Trial Number U1111-1313-4499. Conclusions: This protocol describes a randomized controlled trial comparing BATF with Brief Focal Psychotherapy. The study is designed to generate preliminary evidence on the effects of the intervention in anxiety and depressive symptoms.

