## 2. Methods and Analysis

### 2.1. Trial Design and Registration

This protocol was registered on 6 November 2024, in the Brazilian Clinical Trials Registry (ReBEC) under the identifier RBR-10p45rdg (https://ensaiosclinicos.gov.br/rg/RBR-10p45rdg, accessed on 11 June 2024), where the Statistical Analysis Plan (SAP) is available. The Universal Trial Number (UTN) is U1111-1313-4499.

This protocol was developed in accordance with the SPIRIT 2025 Statement. The completed SPIRIT 2025 checklist is provided as Supplementary Material S1.2.

This study is a single randomized controlled trial with blinded outcome assessment, blinded biomarker analyses, and blinded statistical analysis.

The trial has a 2 × 2 factorial structure, defined by two intervention arms BATF vs. Brief Focal Psychotherapy) and two clinical conditions (anxiety vs. depression), resulting in four analytical cells. Participants will be randomized in a 1:1 allocation to intervention arms, with stratification by clinical condition.

The trial includes two pre-specified analytical phases within the same randomized dataset. Phase 1 is the primary confirmatory analysis, comparing BATF versus Brief Focal Psychotherapy with clinical conditions collapsed. Phase 2 is a pre-specified secondary factorial analysis, evaluating the effects of intervention, clinical condition, and their interaction within the 2 × 2 framework. Both phases were defined prior to trial initiation and registered prospectively, with no adaptive modifications or interim decision-making based on Phase 1 results. Publication of Phase 1 results will not influence recruitment, eligibility criteria, randomization procedures, outcome measures, sample size targets, or statistical methods for Phase 2, which will continue according to the prospectively registered protocol.

The design allows estimation of overall treatment efficacy while also enabling pre-specified evaluation of differential effects across clinical conditions within a single randomized controlled trial framework.

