### 2.7. Randomization and Blinding

Randomization will be performed after eligibility confirmation and informed consent. The allocation sequence will be generated by an independent researcher using a computer-based randomization procedure, stratified by clinical condition.

Allocation concealment will be ensured using sequentially numbered, opaque, sealed envelopes prepared by a researcher not involved in recruitment, assessment, or intervention delivery.

The envelope will be opened immediately before the psychotherapy session by the therapist responsible for intervention delivery. A confidential file linking participant identifiers to randomization codes will be maintained by the independent researcher who generated the allocation sequence and stored securely in a password-protected cloud system.

Participants will be informed that two psychotherapeutic approaches are being compared, without disclosure of allocation or study hypotheses, to minimize expectancy bias. Distinct researchers will be responsible for randomization, intervention delivery, outcome assessment, biomarker analysis, and statistical analysis, with no cross-access to allocation data during the trial.

The same procedures will be replicated in Phase 2.

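### Section 2.4 puts the week-13 scales in a psychotherapy session, which conflicts with the blinded, separate outcome assessment promised elsewhere; who rates MADRS and HAM-A must be reconciled

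*Protocol article*

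**What the plan says.** Three places in the protocol article promise blinded, separate assessment.

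- Abstract: "This randomized, controlled, assessor-blinded clinical trial compares BATF with Brief Focal Psychotherapy".
- Section 2.1: "This study is a single randomized controlled trial with blinded outcome assessment, blinded biomarker analyses, and blinded statistical analysis".
- Section 2.7: "Distinct researchers will be responsible for randomization, intervention delivery, outcome assessment, biomarker analysis, and statistical analysis, with no cross-access to allocation data".

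The Discussion (Section 4) repeats the separation of roles as a strength.

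Section 2.4 describes the visits differently.

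- Week 13: "A follow-up psychotherapy session will be scheduled at week thirteen post-baseline for feedback and the collection of scales and clinical assessments".
- Week 4: "The second BATF session at 4 weeks coincides with the first post-baseline assessment".
- The optional third BATF session is placed nine weeks after the second, "corresponding to the week-13 follow-up visit".
- Those who deliver either therapy: "These professionals are trained to handle the entire psychotherapeutic process, from diagnosis and therapeutic guidance to clinical assessment of progress".

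Three further facts matter. Section 2.5 makes the change from baseline to Week 13 in MADRS (depression) or HAM-A (anxiety) the co-primary outcomes. Section 2.9.4 classes both scales as clinician-administered. Section 2.7 has the therapist open the allocation envelope, and Section 4 accepts that therapists cannot be blinded.

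**The concern.** Week 13 is the primary time point. If its scales are collected in a psychotherapy session, the natural reading is that a therapist is present and may be the rater. That therapist knows the arm. Section 4 concedes that participants cannot be blinded either, and lists possible therapist allegiance bias as a limitation. The blinded rater is therefore the main protection of a clinician-rated endpoint.

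Setting matters as well as rater. The optional third BATF session shares the week-13 visit and is held when therapeutic objectives have not been fully met. An assessor who can see that a treatment session is due that day might infer both the arm and poor progress. Bias that enters through the rating cannot be removed after the data are collected.

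**Working it through.** **Passages side by side**

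| Question | Abstract, Sections 2.1, 2.7 and 4 | Section 2.4 |
|---|---|---|
| Who assesses outcomes? | People other than those delivering therapy, without allocation data | No rater named; therapists described as trained up to assessing progress |
| Where are week-13 scales collected? | Not stated | In a follow-up psychotherapy session |
| What else happens at assessment visits? | Not stated | BATF session 2 at Week 4; optional BATF session 3 at Week 13 |

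Section 2.8 allocates the eligibility interview, biological samples and statistical analysis, but does not say who rates MADRS or HAM-A. The general sentence in Section 2.7 is thus the only direct statement about the rater. Section 2.4 is the only statement about the week-13 setting. A separate rater attending the same visit would satisfy Section 2.7. A reader following Section 2.4 alone could have the therapist collect the scales.

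**The plan's own figure**

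Inputs from Section 2.10: difference 5, SD 11, two-sided alpha 0.05, power 80%, 1:1 allocation. A two-sample t-test with d = 5/11 gives 76.95, so 77 per group. This reproduces Section 2.10.1, which then rounds to 78 per group (156 in total). The sample size is not in dispute here.

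**Illustration of size**

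The documents give no rater-bias figure, so a bias b of 1 or 2 MADRS points between arms is assumed. Other assumptions: SD 11, no true effect, and an unadjusted two-sided 5% t-test.

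Section 2.5 gives each participant only the scale for the primary diagnosis, so a MADRS comparison uses the depression stratum. The size of that stratum is not fixed. An even split is assumed: 156 / 2 arms / 2 strata = 39 per arm.

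Formulas: SE = 11 × √(2/n), and the rejection rate is the power of the t-test at a shift of b/SE.

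| n per arm | SE | b = 1: b/SE | b = 1: rejection rate | b = 2: b/SE | b = 2: rejection rate |
|---|---|---|---|---|---|
| 39 | 11 × √(2/39) = 2.49 | 0.40 | 6.8% | 0.80 | 12.5% |
| 78 | 11 × √(2/78) = 1.76 | 0.57 | 8.7% | 1.14 | 20.4% |

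The 78-per-arm row would apply only if all participants shared one scale, which Section 2.5 rules out. It is an upper comparison. If the depression stratum were tested at 2.5%, as at the first Holm step (Section 2.11), the rates with 39 per arm would be 3.7% and 7.5% against a nominal 2.5%. No SD is given for HAM-A, so no parallel figure is offered for the anxiety stratum.

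**The case against.** The strongest reply is that the only sentence about who assesses outcomes, in Section 2.7, separates assessors from therapists and denies them allocation data. Section 2.4 names no collector. The scales mentioned there could include the self-report PHQ-9, GAD-7 and PSQI. The training sentence is a statement of competence, and ordinary clinical monitoring by a therapist is not trial rating. A blinded assessor at the same visit would fit every passage.

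Much of this stands. A reader might infer that therapists rate the primary endpoint, or that the training sentence gives them that task. The documents do not support either inference: no sentence assigns MADRS or HAM-A to a therapist, and Section 2.7 points the other way.

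A reader might also infer that a week-13 appointment necessarily reveals the BATF arm. That is not supported either. If the follow-up session is held in both arms, its existence reveals little, and Section 2.4 does not say. Ten weekly comparator sessions would end at around Week 10 only if none were missed.

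What the reply does not remove is the wording itself. It places the collection of scales, without exempting the clinician-administered ones, inside a psychotherapy session at the primary time point, and nothing says that the rating is done apart from it.

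**Conclusion.** The point holds as an inconsistency to be reconciled, not as proof of an unblinded rater. The week-13 sentence in Section 2.4, and the alignment of BATF sessions with assessment visits, conflict with the blinding and role separation stated in the Abstract and Sections 2.1 and 2.7. Followed literally, Section 2.4 would expose the clinician-rated primary endpoint to an unblinded rater or setting.

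The size is illustrative only. Under the stated assumptions (SD 11, 39 per arm in the depression stratum, unadjusted 5% test, no true effect), a rating bias of 1 or 2 points would give a false-positive rate of about 7% or 12–13%. If 78 per arm shared one scale, the rates would be about 9% or 20–21%. Whether any such bias would arise is unknown.

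**What to change.** Reword Section 2.4 to agree with Section 2.7:

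- MADRS and HAM-A at Weeks 0, 4 and 13 are rated only by the separate, allocation-blind assessors, outside any therapy session.
- These assessors have no access to the session schedule or session notes.
- Therapists' assessment of progress serves care and is not trial outcome data.

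The section should also say whether the week-13 follow-up session is held in both arms. A separate room, a scripted request that participants not mention their sessions, and a recorded guess of the arm by the rater would be useful but optional extras.

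The cost is protocol wording and slightly more visit coordination. No staff are added, because Section 2.7 already plans separate assessors. Recruitment is due to begin in the fourth quarter of 2026 (Section 2.2), so the change should be made before the first participant is enrolled.

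### Transient adverse events are expected to be under-recorded under BATF, because monitoring relies partly on therapy sessions that are far fewer in that arm

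*Protocol article*

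**What the plan says.** All of this is in section 2.4 of the protocol article unless noted.

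- **What counts as an adverse event:** "any unfavorable psychological, emotional, or clinical occurrence reported by the participant or observed by the therapist during the study period". The examples given are mostly minor and short-lived: passing distress, more anxiety, lower mood, discomfort in sessions.
- **Where monitoring happens:** risks are to be "minimized through continuous clinical monitoring during psychotherapy sessions and follow-up assessments".
- **BATF contacts:** the therapy "will be delivered in a maximum of three sessions". The timing is: "BATF will be implemented on the first day, followed by a second session after four weeks, and a third optional session nine weeks later". The optional third session falls at the Week-13 visit. In addition, "A follow-up psychotherapy session will be scheduled at week thirteen post-baseline for feedback and the collection of scales and clinical assessments".
- **Comparator contacts:** Brief Focal Psychotherapy "may be conducted over a maximum of ten sessions, with sessions occurring once per week".
- **Common assessments:** section 2.5 sets clinical assessments at Weeks 0, 4 and 13 in both arms.

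The article describes no adverse-event inquiry that is structured and scheduled alike in both arms. The Discussion lists unequal intervention dose and possible therapist allegiance as limitations but links neither to the recording of harms.

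**The concern.** Of the two settings named for monitoring, one is balanced between arms and the other is not. A comparator participant who has a bad few days can mention it to a therapist within a week. A BATF participant with the same experience in Week 6 has no scheduled contact until Week 13. The monitoring is called continuous, which sits poorly with a nine-week gap in one arm. The therapist also knows the allocation.

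What is at stake is the reading of harms, not efficacy. The article says that BATF has not been evaluated in a randomised trial and is not yet validated, and section 2.8 sets up no Data Monitoring Committee. Adverse-event counts by arm would be early comparative safety evidence. As collected, they would mix true harm with the opportunity to record it, and the mixing favours the experimental arm. Events that were never recorded cannot be recovered by a later analysis.

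**Working it through.** **The plan's own figure.** The article gives no adverse-event rate, recall period or harms calculation to reproduce. The one figure borrowed below is the Phase 1 group size. A two-sample t-test with d = 5/11 = 0.4545, two-sided 5% and 80% power gives 76.95, so 77 per group, as section 2.10.1 states before raising it to 78.

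**Inputs from the article.** Follow-up is 13 weeks. BATF contacts are at Weeks 0, 4 and 13. The comparator has up to ten weekly sessions, and the Week-13 assessment is common to both arms.

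**Assumptions (not in the article).** True rates are equal and onsets are uniform over 13 weeks. Comparator sessions fall at Weeks 0 to 9. An event is recorded if any contact, session or assessment, follows within w weeks of onset.

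**Formula.** Share captured = (length of the union of the intervals from c − w to c, over all contact times c, within 0 to 13) / 13.

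| w | BATF | Comparator, 10 sessions | Ratio | Comparator, 5 sessions (Weeks 0–4) | Ratio |
|---|---|---|---|---|---|
| 1 week | (1+1)/13 = 15% | (9+1)/13 = 77% | 0.20 | (4+1)/13 = 38% | 0.40 |
| 2 weeks | (2+2)/13 = 31% | (9+2)/13 = 85% | 0.36 | (4+2)/13 = 46% | 0.67 |
| 4 weeks | (4+4)/13 = 62% | (9+4)/13 = 100% | 0.62 | (4+4)/13 = 62% | 1.00 |
| 9 weeks | (4+9)/13 = 100% | 100% | 1.00 | 100% | 1.00 |

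**A second model, for persistent events.** If each contact independently detects the event with probability q, the chance of recording it over k contacts is 1 − (1 − q)^k. For 3 against 10 contacts:

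- q = 0.2: 0.488/0.893 = 0.55
- q = 0.3: 0.657/0.972 = 0.68
- q = 0.5: 0.875/0.999 = 0.88
- q = 0.8: 0.992/1.000 = 0.99

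**What this could do to a table by arm.** Assume that 30% of participants in each arm truly have an event, with 78 per arm. A two-week window gives 0.30 × 4/13 = 9% recorded under BATF and 0.30 × 11/13 = 25% under the comparator. By the normal approximation for two proportions, a 5% test would show a spurious difference about 77% of the time. With a four-week window (18% against 30%) it would do so about 39% of the time. The article plans no such test, so this only illustrates how misleading a plain tabulation could be.

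**After the fix.** If events for the main table come only from inquiries at Weeks 4 and 13 in both arms, the contact times are identical. The expected ratio at equal true rates is then 1.0 for any window that is the same in both arms.

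In none of these scenarios does the ratio exceed 1.

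**The case against.** The best defence is that a definition is being read as a collection procedure. The quoted sentence says what counts as an event, not who asks or when. The full protocol, the case report form and the schedule figure are not shown, and a standard inquiry at Weeks 4 and 13 is not ruled out. That is fair as to missing detail. But the article also says where monitoring takes place, and one of the two settings differs between arms by design.

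Several further points stand and limit the finding:

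- A reader might infer that detection depends wholly on seeing a therapist. The text does not say so: participant report is not confined to sessions, and the Week-4 and Week-13 assessments serve both arms.
- Hospitalisation, emergency referral and similar serious events are unlikely to be forgotten or missed. Deterioration measured on the scales is assessed at the same times in both arms.
- Discomfort arising in sessions needs a session to occur. Part of any excess under the comparator would be a real difference in exposure.
- Ten comparator sessions is a maximum, and the Week-13 follow-up session brings BATF participants to about three contacts.
- The article lists no harms outcome and plans no between-arm test of harms.
- Having the blinded assessor ask about therapy-related events could reveal allocation and put the MADRS and HAM-A ratings at risk. The fix has to allow for this.

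**Conclusion.** The point holds for non-serious, transient adverse events. They are expected to be under-recorded under BATF relative to the comparator even at equal true rates. The size cannot be fixed from the article. Under the assumed windows and a full comparator course, the ratio runs from about 0.2 (one week) through 0.6 (four weeks) to 1.0 (nine weeks or more). With five comparator sessions it runs from 0.4 to 1.0.

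A reader might go further and conclude that BATF harms will look 3.3 to 5 times lower, from 10/3 and 10/2 sessions. The documents do not support that. It needs a one-week detection window that the article does not give and a full ten-session course. The count of two contacts also leaves out the Week-13 follow-up session. With full recall over the nine-week gap the bias disappears.

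Serious events, scale-based deterioration and the efficacy results are largely unaffected. The weakness is worth correcting before recruitment, anticipated for the fourth quarter of 2026, but it does not threaten the primary comparison.

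**What to change.** At the existing Week-4 and Week-13 assessments, give every participant in both arms the same short structured adverse-event questionnaire, covering the whole interval since the last assessment. To protect the MADRS and HAM-A ratings, either have it self-completed alongside the PHQ-9 or GAD-7 and the PSQI, or take it after the rating is locked. In either case the blinded rater should not see it beforehand.

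Use these events for the main between-arm adverse-event table. Report therapist-observed and spontaneously reported events, and all serious events, by arm in a separate table that also gives the number of contacts per arm. That keeps real session-related events visible without treating them as a like-for-like comparison.

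The cost is a short form, a few minutes at two visits that already take place, and a small unblinding risk that the ordering above limits. Session schedules and clinical management are unchanged. The questionnaire equalises the scheduled opportunity to report; it does not guarantee recall over nine weeks, and the report should say so.
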